## Abstract

**Background:**

Germ cell tumors and sex cord stromal tumors are rare cancers of the ovary. They mainly affect young women and are associated with a high survival rate. The standard treatment mainly involves conservative surgery combined with chemotherapy [bleomycin, etoposide and cisplatin (BEP)] depending on the stage and the prognostic factors, as for testicular cancers. As reported in testicular cancer survivors, chemotherapy may induce sequelae impacting quality of life, which has not yet been evaluated in survivors of germ cell tumors and sex cord stromal tumors. The GINECO-VIVROVAIRE-Rare tumor study is a two-step investigation aiming to assess i) chronic fatigue and quality of life and ii) long-term side-effects of chemotherapy with a focus on cardiovascular and pulmonary disorders.

**Methods:**

Using self-reported questionnaires, chronic fatigue and quality of life are compared between 134 ovarian cancer survivors (cancer-free ≥2 years after treatment) treated with surgery and chemotherapy and 2 control groups (67 ovarian cancer survivors treated with surgery alone and 67 age-matched healthy women). Medical data are collected from patient records. In the second step evaluating the long-term side-effects of chemotherapy, a subgroup of 90 patients treated with chemotherapy and 45 controls undergo the following work-up: cardiovascular evaluation (clinical examination, non-invasive cardiovascular tests to explore heart disease, blood tests), pulmonary function testing, audiogram, metabolic and hormonal blood tests. Costs of sequelae will be also assessed. Patients are selected from the registry of the INCa French Network for Rare Malignant Ovarian Tumors, and healthy women by the ‘Seintinelles’ connected network (collaborative research platform).

**Discussion:**

This study will provide important data on the potential long-term physical side-effects of chemotherapy in survivors of Germ Cell Tumors (GCT) and Sex Cord Stromal Tumors (SCST), especially cardiovascular and pulmonary disorders, and neurotoxicity. The identification of long-term side-effects can contribute to adjusting the treatment of ovarian GCT or SCST patients and to managing follow-up with adapted recommendations regarding practices and chemotherapy regimens, in order to reduce toxicity while maintaining efficacy. Based on the results, intervention strategies could be proposed to improve the management of these patients during their treatment and in the long term.

**Trial registration:**

This trial was registered at clinicaltrials.gov: 03418844, on 1 February 2018.

This trial was registered on 25 October 2017 under the unique European identification number (ID-RCB): 2017-A03028–45.

Recruitment Status: Recruiting.

**Protocol version:**

Version n° 4.2 dated from Feb 19, 2021.

## Background

Malignant non-epithelial ovarian tumors are rare cancers that account for less than 20% of ovarian cancers in adults [1]. The main ones are Germ Cell Tumors (GCT) and Sex Cord Stromal Tumors (SCST). They mainly affect young women, are diagnosed early and have a good prognosis and long survival. GCT mainly affects teenagers and young women between 15 and 30 years. They have a good prognosis whatever the stage, with a 10-year survival rate up to 81% [2]. Initial treatment includes conservative surgery (with fertility-sparing for young women) combined with adjuvant chemotherapy [bleomycin, etoposide, and platinum (BEP)], depending on the stage and prognostic factors, as in chemotherapy for testicular cancer [3]. The choice of the optimal chemotherapy regimen for ovarian GCT has been based on standards for testicular cancer. SCST are also rare tumors that occur at any age with a peak incidence between 20 and 40 years. In 70% of cases, they are diagnosed early and have a high rate of remission, with an overall 5-year survival rate of 85% [4]. The main treatment of SCST is also conservative surgery for young women, depending on the tumor extension, associated with the same chemotherapy regimen as for GCT tumors (i.e. BEP) for extensive or recurrent disease.

While follow-up in GCT and SCST ovarian survivors over several years focuses on the risk of recurrence, there is no consensus on follow-up modalities in patients who relapse. Furthermore, the late effects of chemotherapy (metabolic, cardiac, respiratory, renal, hematological disorders, ototoxicity and neurotoxicity) are not routinely investigated. However, follow-up of testicular cancer survivors treated with the same chemotherapy found persistent long-term side-effects of the chemotherapy such as chronic fatigue, cardiovascular and pulmonary disease, neurotoxicity, hypogonadism and a higher risk of secondary cancer. Cisplatin and bleomycin induce alterations in endothelial function and endothelial damage that may trigger vascular diseases [5]. After platinum-based chemotherapy, testicular cancer survivors have a 2-to-3-fold greater risk of cardiovascular disease compared with patients treated with surgery alone or individuals in the general population [6–9]. Raynaud’s syndrome is also a frequent occurrence, with a 2-to-4-fold increased risk after receiving a high platinum dose [10]. In addition, these patients often present a metabolic syndrome, which is a strong predictor of cardiovascular diseases. Metabolic syndrome occurs in 20–30% of long-term testicular cancer patients, and onset is much earlier (3–5 years after treatment) than would be expected in the general population [11, 12]. Other toxicities such as pulmonary toxicity, renal toxicity, ototoxicity and neurological sequelae are frequent and dose-related [13]. According to the available data, the relative risk of a second cancer is approximately doubled after chemotherapy. The estimated cumulative risk of leukemia among testicular cancer survivors who are given etoposide at total doses of less than or equal to 2000 or more than 2000 mg/m2 is 0.5 and 2%, respectively [14].

Testicular cancer survivors have a 6% increased risk of dying of non-cancer causes (infections, cardiovascular disease) after cisplatin-based chemotherapy compared with the general population [15]. Long-term toxicity has been associated with an increased risk of mortality due to pulmonary diseases [16]. Furthermore, the physical effects of chemotherapy and factors associated with the disease such as stress, anxiety and depression have an impact on the quality of life (QoL) of testicular cancer survivors in the physical, psychological, sexual and social domains [17, 18]. Fatigue has been described as one of the most distressing adverse effects of cancer and its treatment. A statistically significant higher frequency of chronic cancer-related fatigue (duration of > 6 months) among long-term testicular cancer survivors (17%) compared with men in the general population (10%) (*P* < .001) has been reported [19]. In the long term, chronic fatigue is strongly associated with poor QoL and numerous psychological and somatic problems. In a longitudinal study exploring chronic fatigue in 812 testicular cancer survivors, prevalence of chronic fatigue increased significantly over time. After 19 years of follow-up, 27% of patients reported fatigue and the risk of chronic fatigue was increased 3-to-4-fold in patients with high levels of neuropathy compared with no neuropathy, 2-to-3-fold for high levels of Raynaud-like phenomena, and 2-to-4-fold for higher levels of anxiety and depression [20]. The late effects of BEP experienced by testicular cancer survivors such as cardiovascular disorders may occur as early as the first year post-treatment [8].

While these issues have received considerable attention in testicular cancer survivors, it is not the case for women treated for non-epithelial ovarian cancers. We hypothesize that the same or similar difficulties and late effects of chemotherapy are also experienced by survivors of ovarian GCT and SCST. In turn, this would have a late impact on their general health, QoL and social and professional integration, as already demonstrated in testicular cancer survivors. The impact of treatment on hormonal status, with consequences on fertility, menopausal status and sexuality, is also crucial in young patients treated for rare ovarian cancer [21, 22]. To our knowledge, very few studies have focused on the impact of chemotherapy on the general health and different domains of QoL of ovarian GCT and CSCT survivors. In a previous study, patients reported significantly greater reproductive concerns and less sexual pleasure than controls. They also more often reported chemotherapy-related effects such as hypertension, hypercholesterolemia and hearing loss [23, 24]. The rate of pulmonary toxicity was greater in SCST patients treated with chemotherapy containing platinum and bleomycin (incidence rate = 7.7% and mortality = 1.8%) [25]. Moreover, in a recent study, hearing disorders were observed in 22% of patients treated with cisplatin-based chemotherapy versus 15% in healthy subjects of the same age [26]. The real impact of chemotherapy on accumulated long-term toxicities and the impact on the different domains of QoL in ovarian GCT and CSCT survivors have not been assessed, and studies to date have been based only on self-reported questionnaires, none of which specifically investigated cardiovascular and pulmonary disorders.

The identification of the long-term side-effect and the impact on QoL encountered by these survivors is thus a prerequisite for proposing and assessing intervention strategies to improve the management of these patients during treatment and over the long term.

## Methods/design

### Objectives

We propose to conduct a large multidisciplinary multicenter case-control study using the INCa French network for rare malignant ovarian tumors TMRG (Tumeurs Malignes Rares Gynecologiques) [27]. The study will explore the needs and difficulties encountered by ovarian GCT and SCST survivors after treatment with surgery (with or without fertility-sparing) and chemotherapy in their daily life, and identify the late effects of chemotherapy.

This case-control study will be conducted in two phases to assess the following:
i)chronic fatigue and several domains of QoL; andii)the long-term medical side-effects of chemotherapy with a focus on cardiovascular and pulmonary disorders, and neurotoxicity.

#### Step 1:

##### Primary objective

The main objective is to assess chronic fatigue in survivors treated for ovarian GCT or SCST with surgery and chemotherapy compared with patients treated with surgery alone and with age-matched healthy women (± 2 years).

The **secondary objectives** are to assess:
Fertility follow-up and parental projects according to age (≤ 45 years);Menopausal symptoms and their impact on QoL;The impact of cancer and its treatments on personal trajectory and professional status (access to work, professional ambition, financial situation, etc.);The different dimensions of QoL including health-related QoL (anxiety, depression, fear of recurrence and sexuality), sleep disturbance, physical activity and living conditions [28] (relationship with partner, family and entourage, consumption of drugs, use of healthcare institutions and social support);Self-reported neurotoxicity and cognitive impairment.

#### Step 2:

##### Primary objective

The main objective is to assess the late clinical effects of chemotherapy with a focus on cardiovascular and pulmonary disorders.

##### Secondary objectives

Metabolic and hormonal disorders, neurotoxicity and ototoxicity, second cancer, Raynaud’s syndrome, and costs of sequelae are also assessed.

##### Design and setting of the study

This is a large two-phase multicenter case-control study (Fig. 1). The study protocol and this manuscript have been written in accordance with standard protocol items, namely recommendations for interventional trials (SPIRIT).

**Fig. 1 Fig1:**
[figure not shown]
STUDY Design. ^1^ GCTSs: Germ Cell Tumor Survivors; ^2^ SCSTSs: Sex Cord Stromal Tumor Survivors; ^3^MFI: Multidimensional Fatigue Inventory; ^4^ FACT-G: General Functional Assessment of Cancer Therapy; ^5^FACT-O: Functional Assessment of Chronic Therapy- Ovarian subscale,^6^ FACT/GOG-Ntx: Functional Assessment of Cancer Therapy/ Gynecologic Oncology Group–Neurotoxicity subscale; ^7^ FACT-Cog: Functional Assessment of Cancer Therapy-Cognitive; ^8^ HADS: Hospital Anxiety and Depression Scale,^9^ ISI: Insomnia Severity Index,^10^ IPAQ: International Physical Activity Questionnaire;^11^ EQ-5D Euroqol questionnaire

### Study participants

**134 adult ovarian GCT or SCST survivors in remission ≥ 2 years after treatment** with **surgery and BEP chemotherapy** (≥ 1 cycle) (recurrence occurs mainly in first 2 years after initial treatment) are compared to **two groups of controls**:
**Patient control group:** 67 adult ovarian GCT or SCST survivors in remission ≥2 years after treatment with surgery alone;**Healthy control group:** 67 age-matched (±2 years) healthy women without cancer and without serious chronic diseases.

Eligible patients of interest and control groups are recruited from the INCa French network TMRG. These patients have been selected by the oncologists of the French cooperative GINECO group (Groupe d’Investigateurs Nationaux pour l’Étude des Cancers Ovariens et du sein). There are 19 participating centers. Healthy women age-matched with patients of interest are recruited from the Seintinelles® network (https://www.seintinelles.com/home). Seintinelles® is a collaborative research platform linking researchers and citizens to accelerate cancer research. Female cancer-free volunteers will be contacted to complete online self-questionnaires. Inclusion and exclusion criteria are detailed in Table 1. A coordinating committee was set up before the conception of the research including the scientific team of TMRG and GINECO and cardiologists.

**Table 1 Tab1:** Study inclusion and exclusion criteria

	Group of interest	Patient control group	Healthy control group
Step 1	**134** ovarian Germ Cell Tumor or Sex Cord Stromal tumor survivors	**67** ovarian Germ Cell Tumor or Sex Cord Stromal tumor survivors	**67** healthy women
Step 2	**90** ovarian Germ Cell Tumor or Sex Cord Stromal tumors survivors	**45** ovarian Germ Cell Tumor or Sex Cord Stromal tumor survivors	**Not applicable**^**a**^
Inclusion criteria	≥ 18 years old	≥ 18 years old	≥ 18 years old
		Age-matched to group of interest (± 2 years)	Age-matched to group of interest (± 2 years)
	Patient treated with **surgery** and **BEP chemotherapy** (≥ 1 cycle)	Patient treated with **surgery alone** (with or without fertility sparing).	
	Patient in remission ≥2 years after initial treatment	Patient in remission ≥2 years after initial treatment	
	Recurrence authorized if remission more than 2 years after end of initial treatment	Recurrence authorized if remission more than 2 years after the end of initial treatment	
	Patient with no other cancers (except basal cell skin carcinoma, breast cancer and cervical cancer)	Patient with no other cancers (except basal cell skin carcinoma, breast cancer and cervical cancer)	Women without cancer or serious chronic diseases
	Patient having signed consent to participate	Patient having signed consent to participate	Healthy women accepted to complete online self-reported questionnaires
Exclusion criteria	Pregnant or breastfeeding woman		
	Psychiatric disorders		
	Major subject to legal protection or unable to express consent		

*BEP* Bleomycin, Etoposide and Cisplatinum

^a^: Healthy control group participated only in step 1 of study (self-reported questionnaire)

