#### Planned analysis

Data analyses will be conducted according to the statistical methods used in paired case-control studies, as follows:
Descriptive analysis of patients’ and controls’ participation and according to sociodemographic and clinical data (including tumor type), quantitative QoL scores and data on living conditions in patients and controls, and then in patients based on medical data related to cancer.Statistical comparison using a univariate and multivariate analysis (ANOVA, or Kruskal-Wallis test, or Mc Nemar χ2 test depending on the nature of the variables and GLM (Generalized Linear Model) model with a Bonferroni correction):Socio-demographic features and comorbidities;Reintegration and sequelae data, then by subgroup (including fertility-sparing);

A prognostic model for predicting QoL or living conditions has been constructed using an adapted model (GLM), taking into account the time since end of treatment and controlling for effect of center.

Medical and biological parameters are the categorical variables. They will be compared between the two groups of patients and then between sub-groups according to time since end of treatment (short term and long-term follow-up) using the χ2 test or the Fisher exact test.

Costs will be compared using the Wilcoxon-Mann-Whitney test. Standard multivariate analyses will be implemented in order to control the potential selection bias. Uncertainties regarding costs of the sequelae will be assessed by probabilistic analysis using nonparametric bootstrap methods: 1000 simulated bootstrap samples will be generated by independent draws. All 95% confidence intervals will be computed. All analyses will be performed using STATA software version 16.0 (StataCorp, College Station, TX).

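### Age-matching of the surgery-alone controls is stated in Table 1 but left out of the abstract, the primary objective and the participants text, and the named tests do not account for age

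*Protocol article*

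**What the plan says.** All places are in the protocol article.

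- **Table 1, inclusion criteria.** The entry "Age-matched to group of interest (± 2 years" (bracket closing after it) stands in the patient control column and again in the healthy control column. The cell for the group of interest is empty, as it should be for the reference group.
- **Study participants, text.** The patient controls are "67 adult ovarian GCT or SCST survivors in remission ≥2 years after treatment with surgery alone", with no mention of age. The healthy controls are "67 age-matched (±2 years) healthy women without cancer and without serious chronic diseases". The recruitment sentence again mentions matching for the healthy group only: "Healthy women age-matched with patients of interest are recruited from the Seintinelles® network".
- **Step 1, Primary objective.** The group of interest is "compared with patients treated with surgery alone and with age-matched healthy women (± 2 years" (bracket closing after it).
- **Abstract, Methods.** The controls are "67 ovarian cancer survivors treated with surgery alone and 67 age-matched healthy women".
- **Pointer to the table.** The participants text adds: "Inclusion and exclusion criteria are detailed in Table 1".
- **Analysis.** The Sample size section names a one-tailed χ² test for each pairwise comparison in Step 1. The Planned analysis section opens with "Data analyses will be conducted according to the statistical methods used in paired case-control studies" but does not say which control group is paired. It names χ² or Fisher tests for the medical and biological parameters of Step 2.

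**The concern.** Three statements name the two control groups side by side and call only one of them age-matched. A reader of the primary objective alone would take the surgery-alone group to be unmatched, whereas a reader of Table 1 would take it to be matched. The analysis section does not settle the point, because its paired methods are not tied to a control group and the sample size rests on an unpaired test for both.

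The group concerned is the important one. Surgery-alone survivors are the only controls who had the same tumours without chemotherapy. They are also the only comparator in Step 2, where Table 1 marks the healthy controls as not applicable. The Step 2 outcomes (cardiovascular and pulmonary findings, hearing, hormones such as AMH) plausibly depend on age.

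The article's Background gives some reason to expect an age difference without matching. Germ cell tumours mainly affect women of 15 to 30 and receive adjuvant BEP according to stage and prognostic factors. Sex cord stromal tumours occur at any age with a peak at 20 to 40, are found early in 70% of cases, and receive BEP when extensive or recurrent. A surgery-alone group could therefore hold more sex cord stromal tumours and older women. This is an inference, as the article reports no age distribution by treatment.

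**Working it through.** **1. The statements side by side**

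| Place | Surgery-alone controls | Healthy controls |
|---|---|---|
| Abstract, Methods | matching not mentioned | matched |
| Step 1, Primary objective | matching not mentioned | matched, ±2 years |
| Study participants, text | matching not mentioned | matched, ±2 years |
| Table 1 | matched, ±2 years | matched, ±2 years |

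No place says that the surgery-alone group is unmatched. Outside Table 1, no place repeats its matching rule.

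**2. The plan's own sample size**

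Inputs from the Sample size section: 25% versus 10%, one-sided α = 0.05, power 80%, ratio r = 2. With p1 = 0.10 (control), p2 = 0.25 and pooled p = (0.10 + 2 × 0.25)/3 = 0.20:

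n(control) = [1.645 × √(0.20 × 0.80 × 1.5) + 0.842 × √(0.10 × 0.90 + 0.25 × 0.75/2)]² / 0.15²
= [0.806 + 0.361]² / 0.0225 ≈ 60.5, so 61 controls and about 121 in the group of interest (122 if 61 is doubled).

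The stated pair is 121 and 61, and power at those numbers is 80.2%. The formula is for independent groups and contains no matching term, so the figure does not depend on which wording is followed. A simulation of 61 matched sets (one control to two chemotherapy patients, stratified one-sided test) gave power of about 81%, 82% and 86% for assumed between-set standard deviations of 0, 0.5 and 1.0 on the logit scale. Matching this group would not undermine the planned size.

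**3. What an age gap could do (hypothetical)**

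The document gives neither an age gap nor an age effect. Assume that the odds of fatigue rise 1.2-fold to 1.5-fold per decade and that the controls are older by 5 or 10 years. The control odds of 0.10/0.90 = 0.111 are multiplied by OR^(years/10). Everything else is as in the plan, with the unadjusted test at 121 versus 61.

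| Gap | OR per decade | Control rate | Power |
|---|---|---|---|
| 0 years | – | 10.0% | 80.2% |
| 5 years older | 1.2 | 0.1217/1.1217 = 10.9% | 74.9% |
| 5 years older | 1.5 | 0.1361/1.1361 = 12.0% | 67.3% |
| 10 years older | 1.2 | 0.1333/1.1333 = 11.8% | 68.8% |
| 10 years older | 1.5 | 0.1667/1.1667 = 14.3% | 50.8% |

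In the opposite direction, suppose controls 10 years younger and no chemotherapy effect. The rates are then 10% versus 8.5% (OR 1.2) to 6.9% (OR 1.5), and the one-sided test rejects in 8.9% to 15.7% of trials instead of 5%.

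**4. Does matching carry through to Step 2?**

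The Sample size section expects around 66% of patients to accept Step 2 (90 of 134 and 45 of 67). Participation is voluntary, so age balance achieved at enrolment in Step 1 need not persist among those who accept. The tests named for Step 2 would not correct for that.

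**The case against.** The strongest reply is that the document already says which text governs. The participants text refers to Table 1 for eligibility, and Table 1 is clear. The prose is silent on matching for the surgery-alone group and does not deny it. It also omits other Table 1 criteria for that group, such as the rules on other cancers and on recurrence, and nobody would take those omissions for competing rules. An abstract and an objective are not eligibility lists. This stands. A reader might infer two different eligibility rules, or that unmatched controls have been enrolled, but nothing in the document shows either.

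A reader might also take the figures in step 3 as the expected loss. They are not. They hold only if the groups differ in age, and they use assumed gaps and assumed age effects. The younger-control case also runs against what the Background suggests, which is older controls.

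It can further be said that the Planned analysis section already lists multivariate analysis and a generalized linear model, including for sequelae data, and that covariate lists usually belong in the statistical analysis plan, which is not shown. This stands in part. Age adjustment may already be intended, but the tests named specifically for these comparisons are unadjusted.

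Finally, age-matching would not make this contrast a pure measure of chemotherapy. By the Background, treatment also follows stage, prognostic factors and tumour extension. That is correct, and the point here is limited to age.

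What remains is that the primary objective itself gives the matching and its tolerance for one of two adjacent control groups and leaves it out for the other. The omission falls on the key comparator.

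**Conclusion.** The inconsistency is real but modest. Table 1 matches the surgery-alone controls on age, and the abstract, the primary objective and the participants text leave this out. Because the text defers to Table 1, it is a fault of statement and not two explicit rules, and correcting the wording alone would be close to editorial.

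The more useful part concerns the analysis. The tests named for chemotherapy versus surgery alone do not account for age in either step. Step 2 rests on this comparator only, and any matching may weaken when about a third of patients decline. Age adjustment is worthwhile whichever wording is followed.

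The sample size of 121 versus 61 is reproduced and unaffected. The size of any bias cannot be derived from the document. The range of 51% to 75% power is an illustration that assumes controls 5 to 10 years older and fatigue odds rising 1.2-fold to 1.5-fold per decade.

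**What to change.** 1. State the Table 1 rule (surgery-alone controls age-matched within two years) in the Step 1 primary objective, the abstract and the participants text, so that all four places agree.
2. In both steps, include age at assessment as a covariate in the chemotherapy versus surgery-alone comparison, for example in a logistic generalized linear model, whether or not matching was achieved.

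The cost is wording in three places and slightly more analysis work. Age must be known anyway to apply the ±2-year and adult-age criteria, so no new data are needed. The sample size does not change.

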**Assessment and comparison of the costs of sequelae in the 2 groups of patients**		
Euroqol (EQ-5D 5 L) questionnaire	Generic measure for clinical and economic assessment	Utility score associated with state of health.

^a^: Clinically significant difference: variation of 5%, ^b^: Responses are categorized into three levels of physical activity: low (<moderate); moderate (3 or more days/week of vigorous activity of at least 20 min/day or 5 or more days/week of moderate activity, or 30 min/day walking) and high (vigorous activity on at least 3 days or 7 days/week of any combination of walking, moderate or vigorous intensity activities). *MFI* Multidimensional Fatigue Inventory -*QoL* Quality of Life, *FACT-G* General Functional Assessment of Cancer Therapy, *PWB* Physical Well-Being, *SWB* Social/family Well-Being, *EWB* Emotional Well-Being, *FWB* Functional Well-Being, *EOC* Epithelial Ovarian Cancer, *FACT-O* Functional Assessment of Chronic Therapy- Ovarian subscale, *FACT-F* Functional Assessment of Chronic Therapy-Fatigue subscale, *FACT/GOG-Ntx* Functional Assessment of Cancer Therapy/ Gynecologic Oncology Group–Neurotoxicity subscale, *FACT-Cog* Functional Assessment of Cancer Therapy-Cognitive, *TOI* Trial Outcome Index, *ISI* Insomnia Severity Index, *HADS* Hospital Anxiety and Depression Scale, *IPAQ* International Physical Activity Questionnaire, *NA* Not Adapted

Volunteers from both patient groups receive information sheets and the different questionnaires from their oncologists during the follow-up consultation or by mail. They are asked to return completed questionnaires anonymously in a stamped preaddressed envelope. A reminder is sent if necessary.

**Patient’s medical data** (date and context of disease diagnosis, treatment modalities, fertility-sparing, second cancer, and comorbidities (focus on cardiovascular diseases, pulmonary and metabolic disorders)) are collected from patient records. For the healthy control group, the website administrator of the Seintinelles network publishes the study information and the questionnaires on their website, and contacts registered healthy women to complete the different questionnaires online.

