**Step 2 = 135 patients**

Assuming around 66% of patients will accept to participate, 90 patients in the group of interest and 45 patients in patient control group are expected to agree to participate.

Assuming 10% of non-assessable participants (around 80 and 40 survivors in the group of interest and control group, respectively), and a proportion of patients experiencing cardiac sequelae varying from 5 to 35% (with a 95% interval confidence) according to literature for testicular cancer [38], it will be possible to estimate the frequency of cardiac sequelae with a precision of 4.8 to 10.5%, in the group of interest and 6.8 to 14.8% in the control group.

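### Second cancer is a Step 2 objective, but the entry rule removes women with any second cancer outside three permitted types, so its overall frequency is understated by an unknown amount

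*Protocol article*

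**What the plan says.** The secondary objectives of Step 2 list "Metabolic and hormonal disorders, neurotoxicity and ototoxicity, second cancer" among the items to be assessed. Under Assessments (Step 1, the paragraph on medical data after Table 2), the items abstracted from patient records include "treatment modalities, fertility-sparing, second cancer, and comorbidities".

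The Background supplies the motive. It reports that "the relative risk of a second cancer is approximately doubled after chemotherapy", and it quotes a cumulative leukaemia risk in testicular cancer survivors of 0.5% at total etoposide doses up to 2000 mg/m2 and 2% above that.

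Table 1 sets the same criterion for the chemotherapy group and the surgery-alone group: "Patient with no other cancers (except basal cell skin carcinoma, breast cancer and cervical cancer". It does not say whether it concerns cancers before the ovarian tumour, cancers active at entry, or any cancer in the woman's history. The remission criterion in the same table does carry a time reference: "Patient in remission ≥2 years after initial treatment".

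For Step 2, "90 patients in the group of interest and 45 patients in patient control group are expected to agree to participate". Table 3 shows enrolment, one questionnaire step and one work-up step, and no later visit.

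**The concern.** Women enter at least two years after treatment, so exposure and part of the risk period for a second cancer already lie behind them. With the data taken from existing records, most of what the study can learn about second cancers is what had happened by entry. The eligibility criterion acts on that same history: a woman whose record shows a cancer outside the three exceptions is not enrolled. An outcome is thus also a reason for exclusion.

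What is at stake is the reading of the result. The Discussion expects the findings to feed recommendations on chemotherapy regimens. A low second-cancer count, or no leukaemia at all, could be taken as reassurance about BEP when the entry rule had helped to produce it. No later analysis of the enrolled women can recover those who were never enrolled.

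**Working it through.** **1. The plan's own Step 2 figure.** The article gives no figure for second cancer. Its Step 2 precision concerns cardiac sequelae at 5% to 35%: "Assuming 10% of non-assessable participants (around 80 and 40 survivors in the group of interest and control group, respectively". The half-width is 1.96 × √(p(1−p)/n).
- n = 80: 4.78% at p = 0.05 and 10.45% at p = 0.35 (stated 4.8% and 10.5%).
- n = 40: 6.75% and 14.78% (stated 6.8% and 14.8%).

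These reproduce and are not in dispute.

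**2. What the entry rule does to the estimate.** Split the second-cancer frequency in each group into permitted types (basal cell skin, breast, cervix) and excluded types: p = p_perm + p_excl. For cancers known at entry, the enrolled women can show only the permitted part.
- Frequency: approximately p_perm is observed instead of p, so the shortfall is p_excl.
- Risk difference, chemotherapy minus surgery alone: the observed difference lacks (p_excl,chemo − p_excl,surgery). If chemotherapy raises the risk of the excluded types, this missing term is positive and the difference is understated.
- Risk ratio: only the ratio for the permitted types can be estimated.

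The document gives no breakdown of second cancers by type, so p_excl cannot be computed. For leukaemia alone the result is exact: none known at entry can appear in either group.

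**3. Illustration for leukaemia.** Inputs are 90 chemotherapy patients (Sample size, Step 2) and risks of 0.5% and 2% (Background). Assume the testicular-cancer risks carry over, and let h be the share of women given more than 2000 mg/m2 etoposide.

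Expected count = 90 × [0.005(1 − h) + 0.02h] = 0.45 + 1.35h.

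| Case | Expected | P(at least one) = 1 − (1 − p)^90 |
|---|---|---|
| h = 0, all at 0.5% | 0.45 | 36% |
| h = 1, all at 2% | 1.8 | 84% |

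The article gives no etoposide doses and requires only one or more BEP cycles, so h is unknown. With the 80 assessable women the range is 0.40 to 1.6. These are counts before allowing for deaths and non-participation, so they overstate what removing the rule would recover.

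**4. How a zero would look.** For 0 of 90, the exact two-sided 95% upper limit is 1 − 0.025^(1/90) = 4.0%; for 0 of 45 it is 7.9%. Reported for leukaemia, such limits would be uninterpretable, because selection rather than sampling fixes the zero.

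**The case against.** **The criterion may be meant more narrowly.** It is undated and could refer to cancers before the ovarian tumour or active at entry. Collecting second cancer from enrolled women's records fits that reading, and an article condenses a longer protocol. If so, the conflict disappears. But nothing in the article says so. Collecting the item is equally consistent with counting the permitted types. As they stand, the objective and the criterion conflict, and at the least Table 1 needs a clarifying phrase.

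**The loss may be modest.** Three types stay countable, and the article gives no distribution by type. This stands. A reader might infer that the overall second-cancer frequency is forced to about zero, but the documents support an exact zero only for excluded types known at entry. A reader might also take 1.8 as the number of leukaemias lost. That requires every woman to have received more than 2000 mg/m2, and it ignores women who died or are too ill to attend, who are missing under any entry rule.

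**No comparison of second cancers is announced.** The objective only says the item is assessed, and Planned analysis compares medical parameters between the patient groups in general terms. A reader might infer that the study intends to claim no excess of second cancers; the article states no such aim. With 90 and 45 women and an illustrative expectation of about one leukaemia, a group comparison would be uninformative even without the exclusion. This stands too, and it is why the objective should be descriptive.

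**Opening eligibility has a price.** Recruitment is under way. A change would mix two entry rules and admit women treated for other cancers, which could confound fatigue and the cardiovascular and pulmonary outcomes. This also stands and decides the choice of fix.

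**Conclusion.** The conflict is real, and it is limited to one secondary objective. As Table 1 is written, second cancers other than basal cell skin, breast and cervical cancer that are known at entry cannot be observed in either patient group. Table 3 shows no later follow-up that would compensate. The overall frequency is therefore biased downwards by an amount that cannot be derived from the document. The between-group difference is biased towards none if chemotherapy raises the risk of the excluded types. The range of 0.45 to 1.8 leukaemias among 90 women is an illustration resting on borrowed testicular-cancer risks, not an estimate of cases lost.

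The conclusion rests on reading the undated criterion as covering the woman's whole history up to entry. A reader might extend the point to the study as a whole, but the Step 1 fatigue objective and the Step 2 cardiovascular and pulmonary objective are unaffected, and the Step 2 precision figures are correct.

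**What to change.** Reconcile the Step 2 secondary objectives with Table 1:

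1. Restrict the second-cancer objective to the three permitted types, report it descriptively by group, and state that no conclusion will be drawn on overall second-cancer or leukaemia risk.
2. Where the TMRG registry or screening records permit, tabulate by chemotherapy yes/no the otherwise-eligible women not enrolled because of a cancer diagnosed after the ovarian tumour. The article does not say how completely these sources record later cancers, so their completeness should be reported with the table.
3. If the criterion was meant to cover only cancers diagnosed before or with the ovarian tumour, state that in Table 1 instead. The restriction in item 1 is then unnecessary, although the numbers would still support description only.

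The cost is a narrower secondary objective, a wording change and one extra tabulation. Sample size and primary analyses do not change. Widening eligibility during recruitment is a trade-off and is not needed to resolve the conflict.
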